**Figure 1 figure1:**
[figure not shown]
Intervention description. ART: antiretroviral therapy; NEG: negative; POC: point of care; POS: positive; SCID-5: Structured Clinical Interview for DSM-5.

All visits will occur in-person in clinic on the same day of the week. Participants will be invited to drop-in for study appointments anytime during clinic hours (9 AM to 5 PM). Visits are estimated to last approximately 20 minutes.

The following key tenets of CM will be adhered to: (1) frequently monitoring the behavior of interest (eg, stimulant use and adherence assessed weekly); (2) tangible, immediate positive reinforcement after confirmation of behavior of interest (eg, POC testing allows for immediate provision of incentives if indicated); and (3) positive reinforcement (ie, incentives) withheld if behavior of interest is not demonstrated [21]. We will use the prize method for reinforcement provision (also known as the “fishbowl method,” established by CM authority [name]), in which participants earn an escalating number of draws from a fishbowl containing paper slips with variable monetary value [28,29]. As specified by distribution of paper slips, patients have a 50% chance of drawing a monetary incentive and 50% chance of drawing an affirmation with an encouraging message (no monetary value; Figure 1). In keeping with this method, participants will receive a “priming draw” at their enrollment visit, in which they draw from the fishbowl until they receive a monetary prize, regardless of their POC results. If a participant misses a visit or does not provide evidence for the target behaviors, the number of draws related to that behavior resets to zero (ie, stimulant positive urine will reset stimulant-related draws to zero).

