### Assessment and Data Collection

All data will be captured and stored using REDCap electronic data capture tools hosted at University of California, San Francisco [35,36]. Most data metrics (described in Table 2) will be extracted from patient interviews during baseline and study visits, although viral loads will be extracted from patient’s electronic medical record.

Baseline assessments (Table 2) will extract patient variables relating to sociodemographics, substance use history, and HIV history, including HIV viral load before participation. We will also collect POC results at baseline (although no incentives will be earned from these results), perform 7-day timeline follow-back to assess baseline frequency of stimulant use, and record visit-related characteristics (length of visit and amount in US $ received through a priming draw; Multimedia Appendix 1) [37].

Visit assessments will assess recent stimulant use and ART adherence, capture POC results, and record visit characteristics (including number of incentives earned). At each visit, we will objectively assess each target behavior through POC testing (used to calculate incentives), subjectively assess stimulant use using 7-day timeline follow-back, and subjectively assess ART adherence using a 3-point Likert scale question (Table 2).

Upon intervention conclusion after 12 study visits, we will record the viral load most proximate to the patient’s last attended visit.

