### Evaluation Frameworks and Outcomes

#### Quantitative Evaluation

We will leverage the RE-AIM (reach, effectiveness, adoption, implementation, and maintenance) framework (Table 3) to quantitatively evaluate feasibility, reach, effectiveness, and intervention implementation.

Per our first study objective, we aim to evaluate the feasibility of implementing this intervention in the safety-net, ambulatory HIV care setting, which we will assess using various domains of the RE-AIM evaluation framework. Our primary outcome will be defined via engagement: 50% CM visit attendance will indicate a threshold for program feasibility. Secondary feasibility outcomes will include number of visits performed, average visit time, and monetary value earned per participant, which map to domains (Table 3). Metrics related to “reach” will assess if the proposed implementation model will be used by a diverse patient population with complex sociomedical needs (as intended), reflecting both the utility and accessibility of this program. “Effectiveness” metrics will seek to establish if the intervention modified the target behavior changes, leading to reduced stimulant use, improved ART adherence, and undetectable HIV viral loads. “Implementation” metrics will describe the costs required to start and maintain this program during the study period (8 months). Our secondary outcome is preliminary effectiveness, which we will determine using proportion of stimulant-negative and tenofovir-positive urine tests, as well as changes in HIV viral suppression before and after participation. We will report missing data and impute missing viral load data as >200 copies/mL.

**Table 3 table3:** RE-AIM (reach, effectiveness, adoption, implementation, and maintenance) framework evaluation of dual-incentive contingency management targeting antiretroviral therapy adherence and stimulant use in ambulatory HIV care.

Dimension	Question	Outcomes
Reach	Will safety-net patients living with HIV and stimulant use disorder enroll in this program? Will they return after enrollment?	Sociodemographics Substance use and HIV histories Proportion of study visits attended
Effectiveness	Will participants reduce stimulant use? Will participants improve tenofovir adherence?	Weekly point-of-care results and 7-d timeline follow-back

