### Participant Interviews

We will create a purposive sample of 14 trial participants, with priority recruitment of at least 7 participants who completed fewer than 50% of CM visits and 7 participants who completed more than 50% of CM visits (Table 4). This sample size will largely depend on the number of participants recruited, but we aim to interview approximately 30% of our total target sample size (ie, 14 participants in a pool of 40). Interviews will seek to (1) understand participant experiences in the primary care–based, stimulant, and adherence-targeted CM intervention and (2) explore how multilevel factors might positively and negatively influence engagement with multitarget CM (eg, role of relationships in the clinic, and concurrent synergistic clinical goals such as gender-affirming surgery, intervention factors such as drop-in visits, and reinforcement schedule, etc). We are secondarily interested in identifying how participant goals for stimulant use reduction are related to HIV management, if at all, and how drivers of stimulant use and additional determinants of health (eg, homelessness, intimate relationships, etc) interact with HIV and stimulant use disorder management.

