### Analysis Plan

#### Quantitative Evaluation

We will analyze reach and implementation metrics (Table 3) using basic descriptive statistics. For effectiveness, we will use descriptive statistics to describe POC results, including the proportion of negative-stimulant and positive-tenofovir tests each week and cumulatively overall and the number of participants that test negative for stimulants or positive for tenofovir at least once. We will also report the average frequency of use as captured by weekly timeline follow-back and compare average use at baseline versus study visit 12 (ie, the final visit) using a paired 2-tailed *t* test. We will use the McNemar test to compare the proportion of participants with HIV viral loads less than 200 copies/mL before and after CM participation.

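### The only formal test of stimulant-use frequency covers visit-12 attenders alone, has no missing-data rule, and is likely to overstate the reduction if people who keep using attend less

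*Protocol article*

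**What the plan says.** Under Analysis Plan, Quantitative Evaluation, the article fixes one inferential comparison of stimulant-use frequency. It will "compare average use at baseline versus study visit 12 (ie, the final visit) using a paired 2-tailed" *t* test. The same sentence adds a description over time: "We will also report the average frequency of use as captured by weekly timeline follow-back". Urine results are summarised descriptively, and the McNemar test concerns viral load.

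The follow-back data come from the visits themselves. Under Assessment and Data Collection, staff will at each visit "subjectively assess stimulant use using 7-day timeline follow-back".

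On missing data, Evaluation Frameworks and Outcomes states: "We will report missing data and impute missing viral load data as >200 copies/mL". No rule is given for follow-back.

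Three other places bear on absence:
- The primary outcome is attendance, and "50% CM visit attendance will indicate a threshold for program feasibility".
- The interview sample plans "priority recruitment of at least 7 participants who completed fewer than 50% of CM visits" (Participant Interviews).
- In the incentive scheme, for anyone who "misses a visit or does not provide evidence for the target behaviors, the number of draws related to that behavior resets to zero" (Intervention, text after Figure 1).

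**The concern.** A paired test needs both values. A participant who misses visit 12 has no second value and is dropped, without the article saying so. The question in Table 3 is whether participants reduce stimulant use, which reads as a question about those enrolled. The test answers it only for those present at one particular visit.

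The two groups may well differ. A stimulant-positive urine earns no stimulant draws, so someone who is still using gains less by coming. If attendance follows success in this way, the attenders' mean change exceeds the mean for everyone enrolled. Apart from bias, fewer pairs mean less precision, while up to 11 further follow-back values per person stay outside the test.

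The article treats viral load differently. A missing value counts as unsuppressed, and for the value after participation "we will record the viral load most proximate to the" last visit that the participant attended. Only the use-frequency test leaves absent people out. The pilot is meant to inform larger trials, so an optimistic estimate of change could be carried into their planning.

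**Working it through.** **Is there a figure to reproduce?** No. The article gives no power, effect size, standard deviation or expected visit-12 attendance for this test. The target of about 40 rests on prevalence. The figures below therefore use stated assumptions and show a range.

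**Inputs from the article.** Target N is about 40 and 37 were recruited. Baseline use is near daily. The test is two-sided and paired, baseline against visit 12.

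**Assumptions.** The share attending visit 12 is *q*. The mean reduction in days per week is *dA* in attenders and *dM* in absentees. The simulation and power figures use a two-sided 5% level; the simulation also uses an SD of change of 2 days.

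**Step 1: bias of the attenders-only estimate.**
- Mean reduction in all enrolled = *q*·*dA* + (1 − *q*)·*dM*.
- The paired test estimates *dA*.
- Overstatement = (1 − *q*)·(*dA* − *dM*).

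With N = 40, *q* = 0.5 (20 pairs) and *dA* = 3:
- *dM* = 0: all enrolled 1.5; overstatement 0.5 × 3 = 1.5.
- *dM* = 1.5: all enrolled 2.25; overstatement 0.5 × 1.5 = 0.75.
- *dM* = 3: all enrolled 3.0; overstatement 0.
- *dM* = 4: all enrolled 3.5; overstatement 0.5 × (−1) = −0.5, so the test understates.

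With *dM* = 0 and other attendance shares:
- *q* = 0.3: 0.7 × 3 = 2.1.
- *q* = 0.7: 0.3 × 3 = 0.9.
- *q* = 0.9: 0.1 × 3 = 0.3.

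**Step 2: effect on the test when mean change is truly zero.** Each person's reduction *d* is normal with mean 0 and SD 2. The chance of attending visit 12 is 1/(1 + exp(−β*d*)), so about half attend. There were 20,000 runs at N = 40.
- β = 0 (attendance unrelated to change): mean estimate 0.0; rejection 4.9%.
- β = 0.5: apparent reduction 0.83 days per week; rejection 49%.
- β = 1.0: apparent reduction 1.22 days per week; rejection 90%.
- β = −0.5 (people who reduced attend less): −0.82 days per week; rejection 48%, in the wrong direction.

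At N = 37, rejection for β = 0.5, 1.0 and −0.5 is 46%, 87% and 46%, with biases within 0.01 days of those above. The normal model ignores the ceiling at 7 days per week, so these figures illustrate a mechanism and do not forecast this trial.

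**Step 3: precision.** The standardized paired effect detectable with 80% power is 0.45 with 40 pairs, 0.66 with 20 and 0.89 with 12. This loss occurs even if absence is random.

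**The case against.** The case on the other side has several parts.

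- **The direction is not certain.** A reader might infer that the test will overstate the reduction. The documents do not support that. Bias is zero if absence is unrelated to change, and it reverses if people who improved stop coming. The incentive argument is also weaker than it looks: the two targets are rewarded separately (Intervention, Description), so someone still using stimulants can earn draws for tenofovir. This stands, and it limits the claim to a likely and conditional one.
- **Half the sample need not be missing.** A reader might infer from the 50% threshold that about half have no visit-12 value. The threshold is a feasibility criterion for visit attendance, not an expected retention rate at week 12. This also stands. Conversely, the Results section reports that the 37 recruits finished the 12-week programme, but not how many attended visit 12, so it does not show the pairs to be complete.
- **The wording might mean the last attended visit.** The gloss on visit 12 could be read that way, which would keep more people. The text nevertheless names visit 12, so this is a further reason to clarify.
- **Little depends on this test.** The primary outcome is attendance. The secondary outcome is defined by urine results and viral suppression, not by this *t* test. Weekly use is also described, and the article promises to report missing data. This stands and lowers the severity.
- **Missing-data detail belongs in the analysis plan.** That is often so. Here, however, the article itself fixes the test, the two time points and an imputation rule for another endpoint, and that combination leaves the absent out.
- **A mixed model can mislead too.** Suppose use falls by *d* between baseline and visit 1 and then stays level. With complete data, the least-squares line over weeks 0 to 12 has slope 6*d*/182, so its fitted change is 12 × 6*d*/182 = 0.40*d*. This stands against a straight-line time trend, not against a model with flexible time.

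**Conclusion.** The point holds in a limited form. As written, the only formal test of stimulant-use frequency estimates change among visit-12 attenders. Absence is foreseen, no rule covers it for this endpoint, and the intermediate visits do not enter the test.

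Overstatement of the reduction among all enrolled is likely if people who keep using attend less. Its size is (1 − *q*)·(*dA* − *dM*), and the article supplies none of the three quantities. Under the assumed 3-day reduction in attenders and 50% attendance, it runs from 1.5 days per week (absentees unchanged) to zero (absentees change equally), and it becomes negative if absentees improve more. At 90% attendance it is at most 0.3 days, provided that absentees on average do not increase their use.

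Severity is minor to moderate. No feasibility or acceptability conclusion depends on this test, but a reader would take it as the pilot's statistical evidence that use fell.

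**What to change.** 1. Keep the paired test as stated. Report its number of pairs and label the result as change among visit-12 attenders. State whether the final visit means visit 12 or the last attended visit.
2. Add a mixed model on all follow-back values (baseline and visits 1 to 12) for every enrolled participant with a baseline value. Enter time as categorical or in another flexible form. Report the baseline-to-week-12 change with its 95% confidence interval. The model uses the earlier visits of people absent at week 12. It assumes that absence is explained by the values observed, so it may reduce the bias without removing it.
3. Add a sensitivity analysis that sets missing week-12 use to the participant's own baseline. This parallels the unfavorable imputation already chosen for viral load. In the notation above it estimates *q*·*dA*. That equals the all-enrolled change if absentees do not change, and together with the paired estimate it brackets the all-enrolled change whenever *dM* lies between 0 and *dA*.
4. Label items 2 and 3 as post hoc, because the Results section says that the quantitative analysis concluded by June 2025.

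The cost is a little more analysis on data already planned for collection, some added text, and probably a smaller reported reduction.

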#### Qualitative Evaluation

To analyze our qualitative data, we will follow the main principles of “scientifically descriptive” thematic analysis as defined by Finlay [38] and further elucidated by Braun and Clarke [39]. Audio recordings will be professionally transcribed into Microsoft Word documents and saved on a secure, password-protected, cloud-based folder that is only accessible to the research team. As traditional qualitative coding is a well-documented, lengthy process, we will use the framework analysis approach to efficiently generate findings with a small team [40,41]. We will first develop a spreadsheet in which we plot the key CFIR constructs outlined in Table 4 across the x-axis and individual research participants across the y-axis. One of the researchers who conducted both patient and care provider interviews (LS) will then review each transcript and copy and paste individual excerpts into the appropriate columns in the spreadsheet. For example, if a patient mentions that they would have trouble keeping an appointment if that was required for participation in the study, this information will be recorded in the “Relative Advantage” column. To keep with the definition of scientifically descriptive thematic analysis by Braun and Clarke [39] and ensure confirmability of findings, a second researcher on the team (AA) will then cross-check a select subset of transcripts and meet with LS to discuss any discrepancies and reach consensus. To enhance reflexivity, the analysts will maintain awareness of how their academic backgrounds may shape data collection and interpretation, ensuring that participants’ experiences with stimulant use disorder and HIV are centered in the analysis.

### Ethical Considerations

This study was approved by the Institutional Review Board at University of California, San Francisco (23-38747). Written informed consent will be obtained from participants before enrollment, consenting to study activities, review of electronic medical records by research staff, and secondary analyses using study data. Consents will be available in English and Spanish (Multimedia Appendices 4 and 5). Participants may opt out of the study at any point.

To maintain participant privacy, any data relating to the study will be stored in either REDCap or an encrypted Box folder hosted by the University of California, San Francisco. Only members of the research team will have access to any participant data stored in REDCap. Study data will not be recorded or linked to the patients’ electronic medical records. Audit of gift cards will be performed by the San Francisco Department of Public Health, per the Controller’s Office protocol. No participants currently incarcerated will be enrolled in this study.

Compensation will be provided for participation in the qualitative evaluation and will consist of a US $50 gift card that can be used at most grocery stores.

## Results

As of September 26, 2024, a total of 37 patients have been recruited and they completed 12 weeks of CM. Analysis of quantitative metrics for RE-AIM evaluation has concluded as of June 2025. Qualitative evaluation has begun, with 10 participants and 7 staff interviewed. Interviews concluded as of January 2025, and analysis is underway.

## Discussion

This work may demonstrate that once-weekly CM targeting both stimulant use disorder and ART adherence can be feasibly implemented in safety-net ambulatory care settings, as defined by the RE-AIM framework. In addition, we may demonstrate through qualitative analysis that such a program is acceptable to both patients and care providers who work in safety-net ambulatory care settings. We anticipate that this single-arm trial will inform any subsequent larger trials investigating the efficacy of offering CM in the HIV primary care setting.

Implementing CM interventions in real-world settings is a critical first step toward reducing morbidity and mortality from stimulant use disorder. Implementation in safety net, ambulatory HIV care—with targeted sampling among patients experiencing homelessness—will help meet the urgent needs of medically complex individuals at high risk for complications of substance use. This protocol offers the opportunity to address syndemic behaviors through one intervention—namely, the related behaviors of stimulant use and ART nonadherence. The success of this pilot would demonstrate the feasibility of offering this evidence-based treatment in HIV ambulatory care and provide a scalable model for implementation in similar safety-net settings. By assessing acceptability through qualitative interviews, we aim to center community voices and align this program with the goals, needs, and lived experiences of people living with HIV and stimulant use disorder.

While abstinence from stimulant use is thought to provide the most clinical benefit (albeit less feasible), use reduction is emerging as an important and meaningful treatment outcome for patients with stimulant use disorder [42]. Moreover, as the field of addiction is evolving to understand addiction as nuanced and multifaceted, we must offer a wider range of treatment implementation options that meet a diversity of patient goals, which may encompass both abstinence-based and reduction-based approaches. In the HIV space specifically, holistic care should address substance use and its related health behaviors, such as reduced rates of ART adherence. Emphasis on reducing stimulant use for people living with HIV and stimulant use disorder may serve as a vehicle to improve overall health among highly susceptible patients.

The use of tenofovir POC assays represents an important advancement, but the inability to rapidly test other forms of ART limits this program to patients on tenofovir-based regimens. This requirement excludes individuals on long-acting ART that are not tenofovir based, although other incentive structures to support injection adherence could be considered. In addition, no POC tests can rapidly quantify stimulant use, thus we rely on indirect methods for assessing stimulant use reduction. While this study targets the enrollment of patients with severe, frequent stimulant use, this program may not be optimally effective for individuals who desire abstinence or with less frequent stimulant use at baseline. Finally, we rely on participant self-report to establish ART nonadherence, which is subject to bias.

This study describes a novel CM program that (1) offers dual incentives targeting the syndemic behaviors of stimulant use and ART nonadherence, (2) uses a novel tenofovir urine assay for POC ART testing, and (3) incentivizes stimulant use reduction. In addition, we describe a protocol for evaluating implementation feasibility in HIV ambulatory care and acceptability to participants and staff. Demonstration of a feasible model that is acceptable to participants with HIV and stimulant use disorder may serve as a first step toward wider use of CM in the safety-net setting and can help meet critical needs in this population.

